## Abstract

Background/Objectives: The “One Health” approach underscores the connection between human, animal, and environmental health, promoting solutions to global challenges like climate change and biodiversity loss. The Planetary Health Diet (PHD) promotes a plant-based diet with organically grown plants to reduce the environmental impact of meat production and decrease the risk of non-communicable diseases (NCDs). The BIOQUALIM project will evaluate the PHD’s effectiveness in preventing NCDs like periodontal diseases and cancers through four inter-related studies. Methods: The clinical study will involve volunteers reducing their meat consumption and incorporating einkorn into their diet, allow for analysis of their interdental microbiota, oral health, general health, and quality of life. The chemical analysis will study nutrients and anti-cancer compounds in einkorn and common wheat varieties. The behavioral study will explore PHD knowledge, attitudes, and behaviors related to PHD. The psycho-social study will evaluate the impact of peer-support workshops on plant-based dietary cooking among post-therapy cancer patients. Results: The results are expected to demonstrate that einkorn varieties possess nutritional properties that, when incorporated into the PHD enriched with einkorn, can enhance health markers. This study will identify barriers to and facilitators of PHD adoption and highlight how peer-support workshops can improve dietary adherence. Conclusions: BIOQUALIM’s transdisciplinary approach will demonstrate the PHD’s role in preventing NCDs.

## 1. Introduction

The “One Health” concept highlights the interdependence of human, animal, plant, and environmental health [1]. It is a holistic approach aimed at addressing global challenges such as antimicrobial resistance, food insecurity, and climate change [2]. The COVID-19 pandemic underscored the need for integrated, cross-disciplinary strategies to prevent, detect, and manage diseases that emerge from disrupted ecosystems [3]. Human health is particularly vulnerable in this interconnected system, with human activities like industrialization and natural resource exploitation playing a significant role in upsetting the balance [4]. These disruptions lead to the emergence of zoonotic diseases, antibiotic resistance, and other health issues. Transdisciplinary collaboration is crucial for addressing these challenges of the 21st century, underscoring the relevance of the “One Health” concept [5].

The Planetary Health Diet (PHD), proposed by the EAT-Lancet Commission, is an integral part of the One Health framework, promoting a diet that supports both human health and environmental sustainability [6,7]. The PHD emphasizes plant-based foods while reducing the intake of animal products, addressing the environmental and health risks associated with meat production [8]. Meat production has lasting effects on the environment, including deforestation, water scarcity, greenhouse gas emissions, and biodiversity loss [9,10]. It also contributes to human health risks through the potential for zoonotic diseases, as 60% of human pathogens and 75% of emerging infectious diseases originate from animals [11]. Biodiversity loss further exacerbates these challenges by weakening ecosystem resilience and limiting opportunities for medical discoveries from nature [12].

Studies indicate that dietary changes are crucial for improving both human health and environmental sustainability [13,14,15,16]. High meat consumption and industrialized foods, prevalent in high-income countries, are linked to higher cancer rates and other non-communicable diseases (NCDs), such as diabetes and cardiovascular conditions [17,18,19]. This is due to the nutritional imbalances caused by diets high in refined grains, salt, saturated fats, and sugars, and low in fruits and vegetables. Meat consumption may promote carcinogenesis, including chronic inflammation, the production of toxic compounds during high-temperature cooking, hormonal imbalance, and consequences of intestinal dysbiosis [20,21,22,23].

Conversely, plant-based diets, including the PHD, Mediterranean diet, and Dietary Approaches to Stop Hypertension diet, offer significant health benefits [6,24,25]. These diets, rich in fiber and low in saturated fat, reduce the risk of obesity [26,27], type 2 diabetes [24,28,29], cardiovascular diseases, and some cancers [29,30,31]. They are also more environmentally sustainable, addressing global health and ecological challenges simultaneously by promoting better dietary practices and reducing environmental impact [32].

Reducing animal proteins and increasing plant proteins in diets, especially in industrialized countries, addresses both public health and environmental concerns [33], with plant proteins being more cost-effective [34]. However, declining biodiversity restricts the variety of available plant protein sources, affecting the ability to meet recommended amino acid intake [35]. Studies have revealed chronic micronutrient deficiencies due to the declining nutritional quality of fruits, vegetables, and grains, driven by reduced crop diversity and industrial agricultural practices [36,37,38]. However, “ancient wheat” species like einkorn, emmer, and spelt, though less common, offer superior nutritional benefits [39,40] and higher levels of bioactive compounds with anti-cancer properties, such as phytosterols [41].

An important area of focus is the link between diet, microbiota, and NCDs. A plant-based diet rich in proteins and fibers and low in sugars and saturated fats, such as the PHD, could help prevent dysbiosis of the intestinal and oral microbiota, a condition linked to NCDs such as periodontal diseases and cancers [19,42,43,44]. Pathogenic oral bacteria, including *Porphyromonas gingivalis* and *Treponema denticola*, are risk factors for periodontal diseases, which are in turn connected to systemic conditions [42]. Controlling microbiota dysbiosis through diet offers the potential to prevent a range of NCDs. While the PHD may help reduce oral dysbiosis, more research is needed to explore its specific role in preventing periodontal diseases [45] and other NCDs [19].

The BIOQUALIM project applies the One Health approach by assessing the PHD’s role in preventing NCDs, particularly periodontal diseases and cancers. The project includes four complementary studies: clinical, chemical, behavioral, and psycho-social (Figure 1). The clinical study will evaluate how the PHD affects oral microbiota dysbiosis and participants’ quality of life. The chemical study will examine the nutritional properties of various wheat species, which will be key components of the PHD for participants in the clinical study and in culinary workshops as part of the psycho-social study. The behavioral study will identify the barriers and motivators for adopting the PHD, which is essential for encouraging broader dietary change. Western societies often face cultural, economic, and convenience-related challenges to reducing meat consumption. Understanding these factors will help design interventions that promote healthier eating habits. The psycho-social study will focus on peer-assisted culinary workshops for cancer patients, helping them adopt the PHD as part of tertiary prevention. These workshops will offer support for participants to learn how to prepare plant-based meals, facilitating long-term behavior change.

Together, the four studies of the BIOQUALIM project aim to provide a comprehensive understanding of how the PHD can contribute to preventing NCDs and improving health outcomes. This aligns with national health initiatives like the French National Environmental Health Plan and the French National Nutrition and Health Program [41,46,47,48,49] and internationals guidelines including those from the WHO [50] and FAO [51], both of which emphasize sustainable eating patterns for human and environmental health. The BIOQUALIM project demonstrates how sustainable dietary practices can address the global burden of NCDs while promoting environmental sustainability.

## 2. Materials and Methods

### 2.1. Main Features of BIOQUALIM Project

The BIOQUALIM project (Figure 2) is a national project supported by a grant from the French National Research Agency as part of the “Investissements d’Avenir ExcellencES” program from France 2030 (SHAPE-Med@Lyon; ANR-22-EXES-0012). This project started in December 2023 and will finish in December 2025.

The BIOQUALIM project will be managed by six French research teams developing a transdisciplinary approach: (i) the laboratory Polymer Materials Engineering (IMP) belonging to the University Claude Bernard Lyon 1, the National Institute of Applied Sciences (INSA), and the National Center for Scientific Research (CNRS, Paris, France), (ii) the Laboratory Systemic Health Pathway (P2S) UR4129 belonging to the University Claude Bernard Lyon 1, (iii) the Cancer Coordination Center (3C-HCL) belonging to the Civil Hospitals of Lyon, (iv) the laboratory Contact and Structural Mechanics (LaMCoS, Lyon, France) belonging to INSA and CNRS, (v) the UMR Territoires and the Department of Geography-Planning belonging to the University Clermont-Auvergne, and (vi) the Center for Social Psychology (PoPS) INSERM U1296 belonging to INSERM and the University Lyon 2. In addition, other partners will contribute: the School of Engineering in Agronomy, Agri-food, and Environment (ISARA, Lyon, France), the National Research Institute for Agriculture, Food, and the Environment (INRAE, Paris, France), and the Center for Applied Botany Resources (CRBA).

This transdisciplinary approach enables the combination of diverse expertise to address the issues from different angles, ensuring a comprehensive and integrated understanding of the challenges related to food, health, and the environment.

The methodological approach is based on action research, with the involvement of a diverse range of stakeholders, including civil society actors (such as a seed conservatory, collectives of partner farmers, collective hospital catering services, and partner patients from Lyon Civil Hospitals) and research teams from complementary disciplines (including chemistry, biochemistry, microbiology, public health, geography, social psychology). This collaborative framework aims to integrate practical and scientific expertise to address the project goals effectively.

### 2.2. Evaluation of the Impact of the Planetary Health Diet on Interdental Microbiota Dysbiosis, a Risk Factor of NCDs Such as Cancer, and on Quality of Life in the General Population (Clinical Study)

#### 2.2.1. Study Design

The “clinical study” will be a single-arm longitudinal comparative pilot study (Figure 3). The protocol will follow the Standard Protocol Items: recommendations for international trials (SPIRIT) [52].

#### 2.2.2. Study Setting

The “clinical study” will be conducted between January 2025 and December 2025 at the HCL (Lyon, France).

#### 2.2.3. Outcomes

The primary outcome will be to compare the number of total bacteria and periodontal pathogens of the interdental microbiota before (T0) and after 3 months (T2) of consumption of a diet enriched in cereal (einkorn) and reduced in meat.

The secondary outcomes will be as follows:-To compare the number of total bacteria and periodontal pathogens of the interdental microbiota before (T0) and after 1 month (T1) of consumption of a diet enriched in einkorn and reduced in meat.-To compare periodontal and oral clinical parameters before (T0), during (T1), and after (T2) the introduction of einkorn into the diet.-To compare general health indicators before (T0), during (T1), and after (T2) the introduction of einkorn into the diet through a consultation and a general medical examination.-To compare quality of life before (T0), during (T1), and after (T2) the introduction of einkorn into the diet through answers to a questionnaire.

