#### 2.2.6. Sample Size

The research hypothesis is part of a superiority test (fewer pathogenic bacteria after changing diet versus before). Referring to the results obtained by Bourgeois et al. [53], with a statistical power of 90% and an expected reduction difference at 3 months of 0.5, 36 participants must be included for significance with a *p*-value < 0.05. Considering an estimated dropout rate of 10%, we plan to include 40 participants. If there are larger dropouts or exclusions, recruitment of additional volunteers will be implemented to ensure the inclusion of 36 participants.

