#### 2.2.7. A Description of the Procedure and Data Collection

The participants will have to change their diet for 3 months. They will reduce their meat consumption by half and will consume einkorn (at least 100 g/day of cooked whole grains, 6 days/week). To achieve this, cooking workshops will be offered during the 3 months of the study.

Three visits will be planned during the study, (T0 (inclusion), T1 (1 month after T0), and T2 (2 months after T1)), to collect the following data:-Microbiological: Sampling of interdental microbiota [54,55,56,57] and real-time PCR to quantify the total number of bacteria and 9 periodontal bacteria. Among them, several are considered cancer risk factors: *Aggregatibacter actinomycetemcomitans*, *Porphyromonas gingivalis*, *Tannerella forsythia*, *Treponema denticola*, *Prevotella intermedia*, *Parvimonas micra*, *Fusobacterium nucleatum*, *Campilobacter rectus*, and *Eikenella corrodens*.-Oral health: Quantitative and qualitative analysis of saliva (GC saliva check buffer, GC, Sucy-en-Brie, France) and measurement of periodontal parameters (Bleeding On Probing (BOP) [58], Gingivitis Index (GI) [59], Plaque Index (PI) [60], Clinical Attachment Level (CAL), and Probing Pocket Depth (PPD) [61].-General health: Body Mass Index (BMI), blood pressure, and abdominal circumference.-Quality of life: MOS SF-36 self-questionnaire validated in French [62].

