#### 2.2.8. Data Analysis

Quantitative data encompassing the entire population will be described, including measures of central tendency and dispersion such as mean, standard deviation, and median. Qualitative variables will be summarized, detailing frequencies and percentages for each level, accounting for missing values without including them in frequency calculations. Absolute and relative frequencies will be calculated for the entire population and at multiple time points (T0, T1, T2). A linear regression analysis will assess the relationship between the interdental microbiome and oral and general health indicators. Paired *t*-tests will compare relative amounts of total and pathogenic bacteria between T0, T1, and T2. Statistical significance will be set at α = 0.05. The analysis of health indices, anthropometric measures, health parameters, and quality of life will employ analysis of variance (ANOVA) to compare trends over time. Linear mixed models could evaluate the impact of dietary intervention on the interdental microbiome, treating time as a random variable and covariates as fixed variables.

Intention-to-treat analyses will be performed on imputed data from all randomized patients using multiple imputation by chained equations, based on a chained Monte-Carlo–Markov algorithm under the assumption of missing data at random.

Descriptive statistics will be calculated with SPSS 12.0 (SPSS Inc., Chicago, IL, USA). Statistical tests (*p*-values) will be calculated with SUDAAN 7.0 (Research Triangle Institute, Research Triangle Park, NC, USA) for repeated measurements (measurements throughout the follow-up period).

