The BIOQUALIM project will have several perspectives: From the point of view of physical chemistry and biology, depending on the “chemical analysis” results, a study of the digestibility of plant proteins according to the type of cooking process used, including a physicochemical study of the evolution of the state of aggregation of these proteins before and after cooking, could contribute to developing suitable and healthier cooking procedures. From the point of view of educational sciences and public health, depending on the “chemical analysis” and “behavioral study” results, awareness programs could be developed to promote the most promising varieties of cereals and pulses which could enrich the cultivated biodiversity in the Lyon region (in organic farming). The implementation of targeted health promotion actions following the study on the extent of socio-spatial disparities in terms of eating habits and knowledge could contribute to reducing territorial health inequalities. In addition, it could be interesting to construct a system for the primary prevention of cancers in public health through education and health promotion of food rich in plant proteins (from the field to the plate). Hence, the results of the behavioral study and the psycho-social study could be used to develop education and training programs (continuing training catalog for health and school establishments). Moreover, an epistemological approach, focusing on the benefits of establishing a pro-literacy environment in the context of food literacy as defined by Slater [79], could be applied. This pro-literacy environment corresponds to an applied philosophy study that aims to more effectively translate scientific findings from several disciplinary fields through active participation and the integration of stakeholders’ concerns and expectations. From the point of view of microbiology, metabolomics, and public health, if the pilot clinical study leads to significant results, a mixed methodology could be used. For the quantitative part, a three-arm randomized controlled trial (control group/meat-depleted diet/meat-depleted diet supplemented with einkorn) will be set up, with analysis of the oral and fecal microbiota (by sequencing) and correlation with diet. For the qualitative part, semi-structured interviews or focus groups could be conducted and analyzed. From the point of view of economy and public health, health economics studies could be carried out to answer questions of social justice about the consumption of cereals and pulses from local organic farming. The results of the BIOQUALIM project will be disseminated through peer-reviewed journals, conferences, and public seminars to ensure broad access to the research outcomes. Throughout the project, we will engage with key stakeholders, including participants, healthcare professionals, and policymakers, to facilitate the translation of the research findings into practice and policy.

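### The clinical study's primary outcome covers two to ten bacterial variables with no decisive one, while N = 36 is sized for a single comparison of pathogenic bacteria

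*Protocol article*

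**What the plan says.** All places are in the protocol article.

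- **2.2.3 Outcomes.** The primary outcome is to "compare the number of total bacteria and periodontal pathogens of the interdental microbiota before (T0) and after 3 months (T2"). Total bacteria and pathogens stand side by side. No single variable, composite or rule for success is given. The T0–T1 comparison of the same bacteria is listed as secondary.
- **2.2.7 Procedure.** The laboratory method is "real-time PCR to quantify the total number of bacteria and 9 periodontal bacteria", so ten quantities are measured per sample.
- **2.2.8 Data Analysis.** Paired "tests will compare relative amounts of total and pathogenic bacteria between T0, T1, and T2", and "Statistical significance will be set at α = 0.05". No order of testing is given.
- **2.2.6 Sample Size.** The hypothesis is "fewer pathogenic bacteria after changing diet versus before". The calculation reads "with a statistical power of 90% and an expected reduction difference at 3 months of 0.5, 36 participants must be included for significance" at p < 0.05, raised to 40 for 10% dropout. Total bacteria are not mentioned. The SD of the change and the sidedness of the test are not stated.
- **3. Results and Discussion.** Follow-on work is conditional: "if the pilot clinical study leads to significant results, a mixed methodology could be used". A three-arm randomised trial is named as its quantitative part. Which result must be significant is not said.

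**The concern.** The stated primary outcome and the hypothesis behind the sample size are different things. One contains total bacteria and pathogens; the other contains pathogens alone. The text also does not settle whether the pathogens are one variable or nine. A reader of the results could not tell from the plan whether the primary outcome had been met if, say, total bacteria fell and pathogens did not, or if one species out of nine changed.

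Two things are at stake. If any significant bacterial result is accepted, 0.05 is the error rate of each test but not of the conclusion. If the error rate is protected across the family, the study no longer has the power that section 2.2.6 claims. In an uncontrolled before–after study, a primary variable chosen after the PCR results are seen cannot be repaired later.

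**Working it through.** **Inputs.** From 2.2.6: difference 0.5, power 90%, p < 0.05, N = 36, dropout 10%. From 2.2.7: one total count and nine species. From 2.2.8: paired t-tests at 0.05. *Assumption:* SD of the paired changes = 1, so 0.5 is a standardised change. Sidedness is not stated, so both cases are shown.

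**1. The plan's own figure.**

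Normal approximation: n = ((z for alpha + z for power) / 0.5)².

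- One-sided: ((1.645 + 1.282)/0.5)² = 34.3, so 35. The exact noncentral t calculation gives 36, with power 90.3% at 36.
- Two-sided: ((1.960 + 1.282)/0.5)² = 42.0, so 43. The exact calculation gives 44, with power 83.1% at 36.
- Dropout: 36 / 0.90 = 40.

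N = 36 is thus reproduced as **one** one-sided paired t-test with SD 1. It would also fit one two-sided test if the SD were about 0.90 (standardised change 0.556). Either way it is the size for one test.

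**2. How many tests the primary outcome holds (T0–T2 only).**

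- Two: total bacteria, and the nine pathogens as one group.
- Ten: total bacteria, and each of the nine species.

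The wording of 2.2.3, 2.2.6 and 2.2.8 fits both.

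**3. Chance of at least one false positive if any significant result counts.**

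Independent tests: 1 − 0.95^k.

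- k = 2: 1 − 0.95² = 9.75%
- k = 10: 1 − 0.95^10 = 40.1%

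Correlated changes, by simulation (n = 36, equal correlation between variables, 20,000 runs):

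| Correlation | 2 tests, one-/two-sided | 10 tests, one-/two-sided |
|---|---|---|
| 0.5 | 8.9% / 9.0% | 25.2% / 29.2% |
| 0.8 | 7.4% / 7.5% | 15.1% / 17.4% |
| 0.9 | 6.8% / 6.8% | 11.9% / 12.7% |
| 1.0 | about 5% | about 5% |

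**4. Power per test at n = 36 if the 5% is protected by Bonferroni.**

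Power = P(noncentral t with 35 df and noncentrality d·√36 exceeds the critical t). For d = 0.5 the noncentrality is 3.0.

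| Basis | alpha 0.05 (one test) | 0.025 (two tests) | 0.005 (ten tests) |
|---|---|---|---|
| One-sided, d = 0.5 | 90% | 83% | 61% |
| Two-sided, d = 0.5 | 83% | 74% | 51% |
| Two-sided, d = 0.556 | 90% | 83% | 63% |

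To regain 90% at d = 0.5, two tests need n = 44 one-sided or 53 two-sided, and ten tests need 63 or 71, before dropout.

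**The case against.** **The number of tests is not stated.** This stands. Section 2.2.7 lists what the PCR measures, not what is tested. A reader might infer that the primary outcome is at least ten co-equal tests, but the article nowhere says that the nine species are tested one by one. Ten is the upper reading and two is the lower. On the lower reading the inflation is modest.

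**The visits do not multiply the primary tests.** This also stands. Because 2.2.8 mentions three visits, a reader might count thirty tests. Section 2.2.3 makes T0–T1 secondary and lists no T1–T2 outcome for the microbiota. The three contrasts cannot be independent either, since the T0–T2 change is the sum of the other two.

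**Correlation.** Counts from the same sample are probably positively correlated, so 40% is a ceiling. Even so, with ten tests the rate is still about 12–13% at a correlation of 0.9.

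**It is a pilot with a tentative outlook.** Partly stands. The study is called a pilot and a proof of concept. The discussion says what could follow and does not say that one significant species would be enough. A false positive would lead to a controlled trial, not directly to an efficacy claim. Yet section 2.2.6 sets a superiority hypothesis, 90% power and p < 0.05, and the outlook hangs on significance.

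**The SAP may handle multiplicity.** An adjustment, above all for secondary tests, may well be there, and its absence from an article is no defect. The mismatch between the primary outcome and the hypothesis that was sized is, however, in this document. An adjustment across the primary variables added elsewhere would lower the power claimed here.

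**Conclusion.** The primary outcome is not reduced to one variable or one success rule, and it does not match the single hypothesis on which N = 36 rests. If any significant result counts, familywise error is up to 9.75% with two tests (about 7–9% at correlations of 0.8 to 0.5). With ten it is up to 40% (about 25–29% at 0.5, and 12–13% at 0.9). Only nearly perfect correlation brings it back to 5%. If the error is controlled by Bonferroni, power at n = 36 falls from 90% to 83% or 61% one-sided, and from 83% to 74% or 51% two-sided, for two and ten tests respectively.

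The power figures rest on an assumed standardised change of 0.5. A reader might set 51% against the planned 90%. That mixes a two-sided corrected test with a one-sided uncorrected one, and part of the gap would be sidedness rather than multiplicity. Only figures in the same row should be compared.

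The documents do not show that the error rate must be far above 5%, nor that one significant species would trigger the next trial. What they show is that the deciding test is undefined, and that the 5% and the 90% cannot both hold for the outcome as worded.

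**What to change.** - **2.2.3:** name one primary variable, the T0–T2 change in a single prespecified pathogen measure that matches the hypothesis in 2.2.6. One option is log10 of the summed count of the nine pathogens. A sum can be dominated by the most abundant species, so another single pathogen measure is equally acceptable if fixed in advance. State the scale as well, because 2.2.3 speaks of numbers and 2.2.8 of relative amounts.
- **2.2.3 and 2.2.8:** make total bacteria and the individual species secondary, reported as estimates with confidence intervals or with Holm-adjusted p-values.
- **2.2.6:** state the sidedness and the SD of the change for that variable, so that N = 36 can be checked.
- **3. Results and Discussion:** tie the condition for follow-on work to the primary variable.

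The change should be made before any PCR results are examined. The cost is wording only, and N = 36 can stand as the size for one test if the stated SD and sidedness support it. The downside is that a signal in total bacteria or in a single species becomes secondary evidence.
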